## Abstract

**Background:**

The main aims of this paper are to describe the setting and design of a Minimal Intervention in general practice for Stress-related mental disorders in patients on Sick leave (MISS), as well as to ascertain the study complies with the requirements for a cluster randomised controlled trial (RCT). The potential adverse consequences of sick leave due to Stress-related Mental Disorders (SMDs) are extensive, but often not recognised. Since most people having SMDs with sick leave consult their general practitioner (GP) at an early stage, a tailored intervention given by GPs is justified. We provide a detailed description of the MISS; that is more accurate assessment, education, advice and monitoring to treat SMDs in patients on sick leave. Our hypothesis is that the MISS will be more effective compared to the usual care, in reducing days of sick leave of these patients.

**Methods:**

The design is a pragmatic RCT. Randomisation is at the level of GPs. They received the MISS-training versus no training, in order to compare the MISS vs. usual care at patient level. Enrolment of patients took place after screening in the source population, that comprised 20–60 year old primary care attendees. Inclusion criteria were: moderately elevated distress levels, having a paid job and sick leave for no longer than three months. There is a one year follow up. The primary outcome measure is lasting full return to work. Reduction of SMD- symptoms is one of the secondary outcome measures. Forty-six GPs and 433 patients agreed to participate.

**Discussion:**

In our study design, attention is given to the practical application of the requirements for a pragmatic trial. The results of this cluster RCT will add to the evidence about treatment options in general practice for SMDs in patients on sick leave, and might contribute to a new and appropriate guideline. These results will be available at the end of 2006.

## Background

### Stress-related mental disorders (SMDs)

Stress results from an imbalance between demands and resources [1]. It is a psychological, physiological and behavioural response by individuals when they perceive a lack of equilibrium between the demands placed upon them and their ability to meet those demands. This response, over a period of time, leads to ill-health [2] and it is important to respect the roles of personal, social, economic, occupational and physical health problems in determining and shaping this psychological disability [3]. Fatigue, tenseness, irritability, apathy, sleeping disorder, emotional instability, rumination and concentration- problems are examples of common symptoms related to stress and a failure to cope with demands while resources (i.e. the abilities to meet those demands) are not sufficient. In addition, some patients with persistent distress go on to develop a psychiatric disorder, notably major depression or anxiety disorder, based on specific vulnerabilities. Plus, persistent distress may give rise to somatic complaints and subsequent somatization [4]. It is clear and evidence- based to treat major psychiatric disorders with medication or counselling, whereas evidence- based interventions for the whole range of Stress-related Mental Disorders (SMDs) are still under development.

### SMDs and sick leave

The societal and financial costs of dysfunction in terms of (long term) sick leave due to SMDs are extensive. In the Netherlands, almost one million workers are entitled to disability benefits (9 percent of the working population), this prevalence is high compared with other countries [5]. About one third of the 9.407 billion Euros in 2004 of the disability benefits in the Netherlands was paid to persons with mental health problems [6]. Whereas only ten percent of those receiving disability benefits have an actual psychiatric disorder, ninety percent is due to what patients and care-providers consider to be SMDs [7]. Furthermore, the composition of the group of workers who receive disability benefit in the Netherlands is changing disquietingly: currently young female employees, mostly with mental health problems, constitute the majority of new cases [8]. Chronicity of SMDs with sick leave is growing, although several studies indicate that SMDs can be treated successfully if they are diagnosed and treated at an early stage[9]. However, for a long time the usual approach to SMDs with sick leave was the reverse: advice to take rest and not return to work before all complaints had disappeared. Last but not least, patients with SMDs being on sick leave definitely cannot be reduced to only an economic problem; of course much personal suffering is involved. Moreover, the value of work is undisputed and in cases of (prolonged) sick leave there is a risk of permanent loss of employment.

### General Practice treatment of SMDs in patients on sick leave

Nearly every employee contacts the GP at the beginning of the sick leave. Most patients having SMDs are managed in primary care, and not referred to specialised secondary care. And despite the fact that mental health problems are common in primary care, GP's may still find it difficult to diagnose and treat them, unless they have a high index of suspicion [10]. Due to the collaborative nature of the doctor-patient relationship in general practice, many GPs may be overly cautious to attribute symptoms to a psychosocial cause. Another issue is an adequate differential diagnosis; many patients in primary care have symptoms related to anxiety, depression, somatization, or all three. In one out of five patients having a SMD there are prominent, although unrecognised symptoms of depression or anxiety, which are associated with a poor prognosis. A further pitfall is that GPs often tend to go along with the patient's request for rest and being left alone. Often GPs advise to go or stay on sick leave, to take rest, seek distraction and relaxation, instead of actively confront and cope with the difficulties. The distress of a lasting crisis combined with existing vulnerabilities may lead to prolonged disability and contribute to the development of serious mental disorders, e.g. depression or anxiety disorders. Earlier research revealed that about 20% of patients having a SMD stayed on sick leave for more than a whole year [11]. Cooperation between GPs and the occupational health care system seems to be in the best interest of all involved and also the preferred way to manage SMDs with sick leave.

### The Minimal Intervention for Stress-related mental disorders with Sick leave (MISS)

Terluin and Van der Klink [12] have outlined an activating intervention for patients having a SMD with sick leave, that already proved to be effective in reducing sick leave by 30% in an occupational health care setting [13]. Taken into account that GPs only have limited time during consulting hours, we developed the Minimal Intervention for Stress-related mental disorders with Sick leave (MISS) for general practice. In the MISS the principle of time contingency is used. Also, parts of more specialised psychological treatments like Cognitive Behavioural Therapy (CBT[14]) and Problem Solving Treatment (PST [15,16]) are incorporated. With respect to the role of gatekeeper in primary care practice, only basic principles of CBT and PST were considered relevant for GPs [17].

The MISS is a prototypical intervention for SMDs with sick leave in general practices, aiming specifically at successful rehabilitation and preventing long-lasting sick leave. By using specific communication and the minimal amount of time necessary, the GP helps the patient on the accurate and time-contingent course. The MISS should take no more than 3 consultations of 10–20 minutes, and consists basically of 5 elements: assessment, education, advice, monitoring and, if necessary, referral.

Assessment implies in the first place to identify patients having a SMD and help them to acknowledge their distress. Second, the GP detects significant depression and anxiety, and propose management steps for these problems separately. The Four-Dimensional Symptom Questionnaire (4DSQ, [18]) is used in the MISS to quantify the level of distress, and to detect symptoms of depression and anxiety. Guidelines from the Dutch College of General Practitioners are available to support the diagnosis and treatment of possible depression and anxiety disorders [19,20]. When physical illness has not yet been ruled out, the patient may have some somatic diagnostic examinations done, next to filling in the 4DSQ.

Education aims at promoting the patient's understanding and acceptance of the cause of the breakdown. Information is given on the normal course after having a SMD with sick leave, in this the patient's own active role is emphasised. The GP also gives information about the role and function of the occupational physician in the health care system. When the diagnosis may not yet be definitive, although the suspicion of a SMD is present, the education is still provided in the first consultation in order not to lose precious time.

Advice is given on coping with the breakdown, making a start with solving the problems, and planning to gradually take up social functioning. The GP underlines the importance of a balance in taking rest and making an active approach towards the problems, like using a rumination session (that is writing down what specifically troubles the patient) one or two times a day for 30–45 minutes. The patient is also advised to schedule necessary activities of daily living, such as children's care and housekeeping. Furthermore the patient is recommended to visit his or her occupational physician without delay, and to explore ways after which it is possible to partially return to work, even when not all symptoms have disappeared.

Monitoring is about ensuring the patient is moving towards the accurate course. This implies a focus on the problems (and possible solutions) in stead of symptoms. The patient has to investigate the specific problems and consider different ways to cope. The switch in the patient's focus has often already occurred before the second consultation; however it should in any case have occurred after four weeks of sick leave.

Referral to specialised care comes into play when there is no evidence of progression after four weeks of sick leave. The GP should realize that the patient is at risk for prolonged sick leave and ultimately loss of employment. A more specialised treatment is necessary since the patient is not likely to benefit from more time off. The GP may refer the patient to a counsellor, social worker or a (cognitive behavioural) psychotherapist, ideally after consulting with the occupational physician.

## Methods

### Objective

The central aim of this pragmatic cluster randomised controlled trial (RCT) is to investigate the effectiveness of the MISS in general practice. Our hypothesis is that GPs who carry out the MISS will be more effective than GPs who perform usual care in reducing the number of days of sick leave, as well as in reducing symptoms of SMDs in patients. Usual care in general practice contains the guidelines on depression [19] and anxiety [20]. In the case of the MISS, GPs are trained in topic- specific knowledge on patients with SMDs on sick leave. Because GPs, who have learned to apply the MISS, cannot be expected to perform this intervention in some patients and treat others as they used to do prior to the training, randomisation at the level of individual patients was not feasible. To avoid possible contamination between the conditions, a cluster design randomising at the level of GPs was chosen. There will be a one year follow up on the patients to assess the outcome measures and factors involved in the process of sick leave and return to work. The study design, protocol and procedures were approved by the Medical Ethics Committee of the VU University Medical Centre.

### Participants

#### GPs

The recruitment of GPs was split up in four different rounds. We approached GPs in two different districts where the Department of General Practice of the VU University Medical Centre has some type of network positioned. A total of 46 GPs signed informed consent.

#### Patients

In order to recruit enough eligible patients, we made use of the computerised patient record system and approached the source population of patients (n = 22.740) by mail. The source population consisted of all primary care attendees (20–60 years) who visited consulting hours of the participating GPs. GP's excluded only patients with very severe psychiatric disorders (mania or psychosis), patients with terminal illness or an inadequate command of the Dutch language. The source population of attendees was asked only to respond when they met our criteria: moderately elevated distress level (measured with 3 questions of the 4DSQ distress scale, [18]), having paid work and being (partially) on sick leave for no longer than three months (see table 1).

Every one or two weeks we approached the source population, until enrolment of a sufficient number of patients from a particular GP was realised. Final recruitment took place by phone survey of the patients who returned the questionnaire and met the criteria. A total of 433 patients (1,9%) who could and also wanted to participate were enrolled (see figure 1). The overall response percentage on our screening method was 51.5%, this was measured in a group of 336 randomly selected attendees. This labour-intensive however highly successful method of screening ensures that we recruited patients having SMDs with sick leave in stead of patients who actually get an intervention for their complaints.

### Intervention at the level of general practitioners

In order to use the intervention, additional training in the MISS was given to intervention GPs by one of the authors (BT), and an occupational physician. This training existed of two times 3,5 hours and 2 times follow-up of 2 hours (total of 11 hours). Skills needed for successful treatment were accentuated. The participating GPs own experiences were evaluated; they were expected to provide case histories and to practice with the different parts of the intervention during the training. Screening of eligible patients started after the MISS group got the second training. When a patient had signed the informed consent (about four weeks after oral informed consent in the telephonic baseline measure), the GP was informed of the participation. Actual application of the elements of the MISS and steps in usual care are measured with a questionnaire.

### Intervention at the level of the patients

During the baseline interview all patients were asked whether they had planned another visit to their GP. If not they were advised to consider this, in order to give the GPs the opportunity to start with an intervention. Even though, it should be noted that neither the GPs were obliged to apply the MISS or any other intervention for mental disorders, nor were the patients obliged to go visit their GPs. No intervention was done on the actual completion or successfulness of the application of the MISS, the present method comprises real clinical practice in primary care.

### Outcome measures

#### Sick leave

The primary outcome measure is defined as: duration of sick leave in calendar days from the first day of sick leave to full return to work, lasting at least 4 weeks without (partial or full) relapse. Variables of the rehabilitation process itself, like the time to first (partial or full) return to work, total days of sick leave in the whole year, and (partial or full) return to work rates after 2, 6 and 12 months, are secondary outcome measures. Sick leave in the past year is considered to be a prognostic factor for our primary outcome measure, as are job content data [21,22].

#### Reduction of SMD symptoms

An important secondary outcome measure is reduction in symptoms of depression, anxiety, somatization and distress, measured with the 4DSQ [18]. Life-events and problems, chronic illnesses and neuroticism [23] are prognostic measures for this outcome. Problem evaluation [24] and coping styles [25] are measured to evaluate the effective components of the MISS: problem- and solution focus skills of patients.

#### Economic evaluation

Cost effectiveness will be evaluated from societal perspective (that is, irrespective of who is paying for the costs to gain an effect) by using the Tic-P [26]. The employers perspective (expenditures for the employer) is represented by the HPQ [27,28]. The EuroQol [29] measures general health state, and as a result quality of life status, that can be compared with a wide range of conditions in health care.

### Data collection

At baseline, patients who entered the study were measured by a phone survey and received a questionnaire by mail. Follow-up measurements, again a phone survey followed by a questionnaire, were scheduled at 2, 6 and 12 months after baseline. All outcomes were measured at the level of the patient, except for the GP interventions and skills. These were reported by the GPs two months after baseline. Moreover, data on received health care were extracted from the medical records after the completion of the one year follow-up.

### Power & sample size

Proportions used to determine the sample size needed, were adopted from a related study completed in the occupational health care setting [13]. In that study, after a period of 3 months 79% in the intervention group versus 64% in the control group had fully returned to work. In order to detect a relevant difference in survival analysis on our primary outcome measure, nQuery Advisor [30] was used to calculate the sample size. With a power of 80% at a 0.05 level two-sided log-rank test for equality of survival curves between the MISS group proportion still on sick leave of 0.21 and a usual care group proportion of 0.36 at the given time of 3 months, the sample size needed in each group was 126 (with a constant hazard ratio of 1.528). Taking into account an intracluster correlation coefficient (ICC) of .025 (clustering effect in our groups is not presumed to be large) for randomisation at GP level and 7 patients per cluster (GP), a total of 290 patients are needed. Assuming a dropout rate of 30% (approximately 10% at each follow up), inclusion of a total of 415 patients is necessary.

### Randomisation

Randomisation took place at the level of GPs, after each of the four recruitment moments and after the GPs signed informed consent. Because balance between groups in size and characteristics was presumed all four times GPs were randomised, no blocking or stratification was used. We developed the following procedure to conceal allocation. The names of the GP's (and dummy in an uneven group) were put on a list of which the order was subsequently randomised by one person ([name]). Another person (BT) independently drew up a randomised list of codes (1 = MISS group and 2 = control group) with an equal number of '1' and '2' codes up to the number of GPs being randomised. Finally, these two lists were brought together and the first GP on the list was allocated to the group indicated by the first code; and so on. As a result, 24 GPs were allocated to the intervention (MISS) group and 22 GPs were allocated to the control (usual care) group.

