### Statistical methods

First of all, baseline similarity between the MISS and usual care groups will be examined, and baseline characteristics of drop outs and completers will be compared. Cox regression analyses will be used to investigate the intervention effect, by analysing differences in outcome with survival analysis of the primary outcome measure between the MISS and usual care group. To correct for misclassification of patients and severity of complaints (inclusion is only by level of distress with sick leave), and as a consequence to avoid bias in the effect, baseline measures of psychological symptoms (by means of the 4DSQ [31] & PRIME-MD [32]), as well as medical records will be examined. Additionally, subgroup analysis can be done by level of severity of complaints.

Linear and logistic multilevel analyses will be used to investigate the intervention effect on all secondary outcome measures: rates of return to work, psychological symptoms, problem experience and coping style. Also, longitudinal multivariate analysis will be used to examine differences in improvement in all secondary outcome measures between the treatment groups. Analysis will be performed on an intention-to-treat basis and intra-class-correlation will be calculated to correct for possible clustering of observations. Levels included will be: repeated measures, patients and GPs. Subgroups for analysis will be modelled by the prognostic factors mentioned.

Costs will be measured and valued from a societal perspective. Mean direct and indirect medical costs (measured with the Tic-P[26]), costs of productivity loss due to sick leave (measured with the WHO HPQ[28]) and total costs will be compared between both groups. Confidence intervals around mean differences will be estimated with bootstrapping methods. With regard tot the primary outcome, sick leave, a cost benefit analysis will be performed, in which costs of productivity loss due to sick leave will be compared with direct en indirect medical costs.

A cost-effectiveness analysis will be performed to assess the incremental costs per unit improvement on the 4DSQ [18]. Bootstrapping methods will be used to estimate the confidence interval for the cost-effectiveness ratio and to a draw cost-effectiveness plane. Similarly, utility assessed with the EuroQol [29] will be used to estimates the incremental costs per Qualy gained in a cost-utility analysis.

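### The article denies any blocking or stratification, but its procedure is a permuted block within each of four recruitment rounds; correct the sentence and account for round in the models

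*Protocol article*

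**What the plan says.** All the relevant statements on allocation are in the Methods of the protocol article.

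- On recruitment (Participants, GPs): "The recruitment of GPs was split up in four different rounds".
- On timing (Randomisation): "Randomisation took place at the level of GPs, after each of the four recruitment moments".
- On restriction (Randomisation): "Because balance between groups in size and characteristics was presumed all four times GPs were randomised", and therefore "no blocking or stratification was used".
- On the code list (Randomisation): it was drawn up "with an equal number of '1' and '2' codes up to the number of GPs being randomised". The list of GP names was padded ("and dummy in an uneven group") so that it could be matched to that code list.
- On the result (Randomisation): "24 GPs were allocated to the intervention (MISS) group and 22 GPs were allocated to the control (usual care) group".

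Statistical methods says of the primary outcome that "Cox regression analyses will be used to investigate the intervention effect". For the multilevel models it lists repeated measures, patients and GPs as the levels. Recruitment round is not mentioned in that section, either as a term to include or as one to leave out.

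**The concern.** The label and the method disagree within one paragraph. A shuffled list with a fixed, equal number of codes for each arm is a permuted block. Drawing a fresh list of that kind for each round makes round a stratum. Balance in numbers was therefore forced by the code list, whereas the article says that it was only presumed.

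This matters in two ways. First, the article sets out to show that the trial meets the requirements for a cluster randomised trial, so the description of the allocation should be right. Second, an analyst normally accounts for the factors that restricted the randomisation, and one who relies on the sentence would see no reason to do so. If outcomes differ between rounds, for example because the rounds fell at different times, that variation stays in the error term although the design has already balanced it across arms. The standard error of the treatment effect is then larger than the design warrants.

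**Working it through.** **1. What the procedure implies for the allocation.** In an even-sized round, equal codes give a difference of 0 between arms. In an odd-sized round, the dummy takes one code and the difference is exactly 1. Over four rounds the total difference cannot exceed 4. The total of 46 GPs is even, so the number of odd rounds is 0, 2 or 4.

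**2. The article's own figure.** 24 + 22 = 46, a difference of 2. This can arise under the procedure with 2 or 4 odd rounds; the probability of a difference of 2 in either direction is 0.50 in both cases. With no odd rounds the split would be 23:23. The reported split is therefore compatible with the procedure.

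**3. Sample size is not touched.** The chain in Power & sample size reproduces:
- Hazard ratio: ln(0.21)/ln(0.36) = 1.528.
- Freedman's formula gives 180 events; 180/(1 − (0.21 + 0.36)/2) = 251.7, hence 126 per group.
- Design effect: 1 + (7 − 1) × 0.025 = 1.15; 252 × 1.15 = 289.8, hence 290.
- Dropout: 290/(1 − 0.30) = 414.3, hence 415.

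Round enters none of these steps.

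**4. How much precision is at stake.** This is a GP-mean approximation to the planned models, with total patient variance set to 1.
- Inputs from the article: ICC 0.025; 433 patients and 46 GPs, so 433/46 = 9.4 patients per GP.
- Variance of a GP mean: 0.025 + 0.975/9.4 = 0.129.
- Between-GP share: 0.025/0.129 = about 19%.
- Assumption, not in the article: round explains 5–10% of between-GP variance. Adjustment then removes 0.05 × 19% to 0.10 × 19%, that is, about 1–2% of the variance of a GP mean, or about 0.5–1% of the standard error.
- Cost: with round as a covariate, residual degrees of freedom fall from 44 to 41 and the critical t value rises from 2.015 to 2.020, about 0.2%.

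On this assumption the net gain is under 1% of the confidence interval width. The ceiling, if round explained all of the between-GP variance, is the 19% share itself.

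**5. Direction of the error if round is left out.** GP-level outcomes were simulated under the described allocation with no treatment effect, and tested at 0.05 with a linear model (5,000 simulated trials per row). Assumed inputs: rounds of 12, 12, 11 and 11 GPs, 9.4 patients per GP, ICC 0.025, and a round effect added on top, in patient-level SD units.

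| Between-round SD | Type I error, round omitted | Type I error, round as covariate |
|---|---|---|
| 0 | 0.046 | 0.047 |
| 0.1 | 0.042 | 0.048 |
| 0.2 | 0.024 | 0.048 |
| 0.3 | 0.009 | 0.051 |

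The Monte Carlo standard error near 0.05 is √(0.05 × 0.95/5000) = 0.003. Omitting round never raises the error rate above nominal and lowers it as rounds diverge. For scale, the 5–10% assumption in step 4 corresponds to a between-round SD of √(0.05 × 0.025) = 0.035 to √(0.10 × 0.025) = 0.05, which lies between the first two rows. An SD of 0.2 means a variance of 0.04, more than the whole planned between-GP variance of 0.025, so the last two rows are stress cases.

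**The case against.** The best defence is that nothing is hidden. The article sets out the timing, the equal codes and the dummy, so a careful reader can see the restriction. The sentence may have been meant to say only that no smaller blocks were used within a round and that GPs were not stratified by their characteristics. That meaning is plausible, but it is not in the text, and the label remains wrong for the method described. The allocation itself is sound and complete, so the correction concerns reporting and analysis.

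The second line of defence also has force. The article is silent on round but does not exclude it. The listed levels describe the hierarchy of the multilevel models and leave room for a fixed covariate, and an article may leave Cox covariates to a fuller plan. So a reader might infer that the analysis has decided to ignore round; the article does not say that. What stands is that no analysis named in it includes round, while the sentence on allocation points away from including it.

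Other stronger readings also fail:
- A reader might take standard errors that do not match the design to mean invalid tests. Step 5 shows the opposite direction: the tests stay valid and become conservative.
- A reader might take the 24:22 split as confirming the restriction. It does not: unrestricted 1:1 randomisation of 46 GPs gives a difference of 2 or less with probability 0.34. The evidence is the described procedure.
- A reader might worry about a permutation test with the wrong reference set. The article plans none.
- A reader might apply the 5–10% to the whole error of a GP mean. It applies only to the between-GP part, about 19% of that error.
- A reader might tie rounds to districts or training sessions. The article mentions two districts but does not link either to rounds.

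**Conclusion.** The sentence contradicts the procedure in its own paragraph: allocation was by permuted block within each recruitment round, with at most one GP of imbalance per round. This rests on the text alone and needs no assumption.

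The consequence for the analysis is modest. Accounting for round is worth doing because the trial randomised within it and it costs almost nothing. The likely gain is about 1–2% of the variance of a GP mean. That figure depends on an assumed 5–10% share of between-GP variance, the planned ICC of 0.025, equal cluster sizes of about 9.4, and a GP-mean approximation to the Cox model. Round sizes and round effects are not given, so the gain cannot be computed from the article. The point gives no reason to doubt the protection against false positives or the sample size.

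**What to change.** 1. In Randomisation, replace the denial with a statement that GPs were allocated in equal numbers to the two arms within each of the four recruitment rounds (to within one GP in odd-sized rounds), with no further restriction inside a round and no stratification by GP characteristics, if that is what was done. Giving the round sizes would complete the description.
2. In Statistical methods, include recruitment round in the primary Cox analysis as a stratum or covariate, and as a fixed effect in the multilevel models for the secondary outcomes. If a fuller analysis plan already does so, a sentence saying so is enough.

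The cost is a change of wording and one factor that should be known from the allocation lists. As a covariate, round uses 3 degrees of freedom among 46 GPs. No new data are needed and the sample size stays as it is.
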